**Methods:**

This prospective, single-center, observational cohort study will screen all patients receiving CRRT for eligibility. General clinical information will be collected before commencing CRRT treatment. Patients will be randomly assigned to either the continuous veno-venous hemofiltration (CVVH) or continuous veno-venous hemodialysis (CVVHD) group and switch to the alternative mode in the subsequent treatment session. Pre-filter and post-filter ionized calcium, systemic total and ionized calcium, and effluent total calcium will be measured 2 h after the initiation of CRRT. Electrolyte levels, arterial blood gases, hourly citrate dose, and total citrate dose will be recorded every 6 h until the end of CRRT. The primary outcome is the difference in ionized calcium concentrations at each site over time between the two modes.

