**Figure 1. F0001:**
[figure not shown]
Theoretical trends of ionized calcium movement in different renal replacement therapies. Panel A: In hemofiltration, solute and solvent move from blood to effluent across a semipermeable membrane (dotted line) in response to transmembrane pressure. For citrate-anticoagulated blood, iCa concentration (solid dots) should be identical on both sides of the membrane, with a typical iCa of approximately 0.4 mmol/L. Panel B: In hemodialysis, the iCa concentration of calcium-containing dialysate (approximately 1.5 mmol/L) is much higher than the level of iCa in the citrate anticoagulated blood (approximately 0.4 mmol/L); therefore, iCa moves with the concentration gradient from the dialysate to the blood, resulting in an increase in post-filter iCa, which in turn may affect the efficacy of citrate anticoagulation.

However, the effect of citrate on post-filter iCa concentrations was investigated in the context of calcium-free replacement solutions in previous studies [25,26]. There is little data to show whether different CRRT modes can affect post-filter iCa concentrations during RCA-CRRT using calcium-containing replacement fluid. We hypothesize that a dialysis-based CRRT mode would increase post-filter iCa concentrations and citrate requirements. The present study aims to explore the influence of different CRRT modes on the post-filter iCa concentration in patients receiving RCA-CRRT using calcium-containing replacement fluid.

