### CRRT parameter setting and management

PrismaFlex (Baxter Investment Co., Ltd, Chicago, IL) CRRT device and AN69 ST150 hemofilters (Baxter Investment Co., Ltd, Shanghai, China) will be used. Vascular access will be established by inserting a double-lumen catheter (SCW Medication Ltd, certification number: 20173664588, 12 Fr, 20 cm) into either the femoral or internal jugular vein. CRRT will be ended for any of the following reasons: achievement of therapeutic goals; coagulation of the filter; transmembrane pressure continuously > 250 mmHg; or continuous treatment for 48 h (to replace pipeline and filter).

This study is a before-after design in the same patient; each patient will receive both continuous veno-venous hemofiltration (CVVH) and continuous veno-venous hemodialysis (CVVHD) at least once. Patients will be initially randomized into either the CVVHD or CVVH groups and then crossed over to the other group during the second CRRT session. Regardless of whether CVVH or CVVHD is used, the initial settings will be as follows: blood flow rate of 150 ml/min, 4% sodium citrate flow rate of 230 ml/h, 10% calcium gluconate infusion rate of 10 ml/h, and a 5% sodium bicarbonate infusion rate (ml/h) of dialysate/replacement fluid × 0.0625 − 120. The therapeutic dose will be 30 ml/kg/h depending on the mode investigated, that is, a dialysate rate (ml/h) of 30 ml × body weight (kg) in the setting of CVVHD; on the other hand, the replacement fluid rate (ml/h) will be 30 ml × body weight (kg) in the setting of CVVH.

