The clinician will assess whether to adjust the CRRT parameters based on arterial blood gas and post-filter iCa concentration two hours after the start of CRRT. No adjustment of the citrate dose is required, and post-filter iCa levels will be monitored every four to six hours if the therapeutic goal of anticoagulation is achieved (post-filter iCa concentration 0.20–0.4 mmol/L). If anticoagulation is not achieved, the citrate infusion rate will be adjusted according to Table 1, and post-filter iCa levels will be monitored every two hours until the therapeutic goal is achieved. The goal of systemic iCa will be between 1.00 and 1.20 mmol/L. The 10% calcium gluconate infusion rate will not be adjusted, and arterial blood gas will be monitored every four to six hours if serum iCa concentration reaches the target. The calcium gluconate infusion rate will be adjusted according to Table 2, and arterial blood gas will be monitored every two hours until the target is reached if serum iCa concentration does not reach the target.

**Table 1. t0001:** Adjustment of 4% sodium citrate infusion rate according to post-filter ionized calcium level.

Post-filter iCa (mmol/L)	Change in citrate infusion rate
<0.2	20ml/h ↓
0.2–0.4	No change
0.41–0.45	10ml/h ↑
>0.45	20ml/h ↑

**Table 2. t0002:** Adjustment of calcium gluconate infusion rate according to systemic ionized calcium level.

Systemic ionized Ca^2+^ (mmol/L)	Change in 10% calcium gluconate infusion rate
>1.35	5ml/h ↓
1.2–1.35	2ml/h ↓
1.0–1.2	No change
0.91–0.99	2ml/h ↑
0.86–0.90	5ml/h ↑
0.75–0.85	7.5 ml/h ↑
<0.75	10ml/h ↑

If circuit clotting is detected, the circuit will be discontinued immediately to ensure patient safety. All clotting events will be documented in detail, including the time of detection, last recorded post-filter iCa level, circuit running time before clotting, and citrate dose at the time of clotting. The attending physician will then evaluate the patient’s clinical condition to determine whether immediate CRRT re-initiation is necessary or if CRRT can be temporarily discontinued until the next scheduled treatment. If clinical assessment indicates the need for immediate CRRT continuation, a new circuit will be initiated following the standard protocol. Given the short half-life of citrate, the time required for circuit replacement is believed to be sufficient to eliminate any carry-over effects.

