### Study objectives

The primary objective is to evaluate trends in post-filter iCa2+, pre-filter iCa effluent iCa2+ and total calcium, systemic iCa2+, and total calcium concentration over time in different RCA-CRRT modes.

The secondary objectives are to analyze the amount of citrate used in different modes to achieve the desired anticoagulant effect in current clinical practice, and to assess the incidence of new-onset metabolic complications (hypercalcemia, hypocalcemia, metabolic acidosis, metabolic alkalosis, citrate accumulation, hypernatremia, hyponatremia). The incidence of metabolic complications will be calculated as the number of new-onset metabolic complication events per 100 CRRT days. In this study, citrate accumulation is defined as the presence of a total serum calcium/ionized calcium ratio > 2.5.

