### Statistical analysis

Data will be analyzed using SPSS 23.0 statistical software (IBM Co., NY). Continuous variables will be presented as means and standard deviations (for normal distribution) or medians and interquartile ranges (for non-normal distribution). A paired *t*-test will be used for normally distributed variables, and the Wilcoxon signed-rank test will be used for non-normally distributed variables. Categorical variables will be presented as numbers and percentages and analyzed using the *χ*^2^-test or Fisher’s exact tests, as appropriate. For the crossover design, we will specifically examine both carry-over and period effects. The carry-over effect will be assessed by comparing the sum of the outcomes between sequences using a t-test or Mann-Whitney U test depending on data distribution. The sequence of interventions will be randomly assigned to minimize potential period effects. A two-sided *p* < 0.05 will be considered a statistically significant difference.

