There are several limitations to this study. First, it will only compare the differences in iCa changes between CVVH and CVVHD at each time point, thus not providing information on iCa concentration changes in combined modes (e.g. continuous veno-venous hemodiafiltration, CVVHDF) with varying dialysate and replacement fluid ratios. In other words, this study focuses exclusively on CVVH and CVVHD modes. While CVVHDF is increasingly used in severe AKI patients, we chose CVVH and CVVHD as our initial investigation platforms to establish the fundamental principles in more controlled settings. This strategic approach will serve as a stepping stone for future studies investigating more complex CRRT modalities such as CVVHDF. Second, plasma citrate concentrations will not be measured in this study, making it impossible to directly compare differences in plasma citrate concentrations.

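### Paired tests at each time point cannot carry a trend outcome when sessions end at different times, partly for reasons tied to the outcome

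*Protocol article*

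**What the plan says.** **Outcome.** The Abstract (Methods) states: "The primary outcome is the difference in ionized calcium concentrations at each site over time between the two modes". Study objectives agrees: "The primary objective is to evaluate trends in post-filter iCa2+, pre-filter iCa effluent iCa2+ and total calcium", together with systemic calcium, followed over time.

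**Comparison.** The limitations paragraph of the Discussion says the study "it will only compare the differences in iCa changes between CVVH and CVVHD at each time point". For continuous variables, Statistical analysis names a paired t-test if the data are normal; otherwise "the Wilcoxon signed-rank test will be used for non-normally distributed variables". It names no longitudinal method.

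**Length of observation.** Under CRRT parameter setting and management, a session ends for any of these reasons: "achievement of therapeutic goals; coagulation of the filter; transmembrane pressure continuously > 250 mmHg; or continuous treatment for 48 h". On clotting: "If circuit clotting is detected, the circuit will be discontinued immediately to ensure patient safety". The physician then decides whether a new circuit starts at once or treatment waits. Data collection and follow-up has 6-hourly recording stop when CRRT stops.

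**Link between outcome and circuit end.** The Figure 1 legend describes calcium moving from dialysate to blood in hemodialysis, "resulting in an increase in post-filter iCa, which in turn may affect the efficacy of citrate anticoagulation".

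**The concern.** A paired test at a given hour can use only patients who have a reading at that hour in both the CVVH and the CVVHD session. Once either session has ended, the patient leaves the comparison, and the readings already taken in the other session at later hours go unused. The set of patients therefore changes from one time point to the next, so a sequence of such tests does not describe a trend in a fixed group.

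The loss may also not be random. If higher post-filter iCa weakens anticoagulation and CVVHD raises post-filter iCa, both as the protocol hypothesises, a session's end can depend on mode and on the outcome itself. This happens within the sessions of patients who do cross over. It is separate from patients who never reach a second session.

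At stake are the later time points and the trend, which is what the primary objective asks for, and the power available there.

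**Working it through.** **1. Reproduce the sample size.** Inputs from Sample size: means 0.44 and 0.305 mmol/L, SD 0.2, alpha 0.05, beta 0.10. Two-sided testing is from Statistical analysis.

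- Difference: 0.44 - 0.305 = 0.135. Standardised: 0.135 / 0.2 = 0.675.
- Normal approximation: ((1.960 + 1.282) × 0.2 / 0.135)² = 23.06, so 24 pairs.
- Paired t-test (noncentral t, noncentrality 0.675 × √n): power 0.899 at n = 25 and 0.911 at n = 26.

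The stated 26 reproduces if 0.2 is the SD of the paired differences (equivalently, SD 0.2 per mode with within-patient correlation 0.5). It counts complete pairs at one time point.

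**2. How many pairs can be lost.** Thirty patients leave room for 30 - 26 = 4. A pair survives only if both circuits run. If circuit lives are independent, pairs = 30 × S(CVVH) × S(CVVHD), where S is the share of circuits still running. At 0.93 in each mode: 30 × 0.93 × 0.93 = 25.9.

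The documents give no circuit survival, so the range below is assumed. It holds the difference at 0.135 and the SD at 0.2, and counts no replacement circuits.

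| S CVVH / S CVVHD | Pairs of 30 | Power |
|---|---|---|
| 0.95 / 0.95 | 27 | 92% |
| 0.90 / 0.80 | 22 | 86% |
| 0.80 / 0.70 | 17 | 74% |
| 0.70 / 0.50 | 10 | 48% |
| 0.60 / 0.40 | 7 | 33% |

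**3. Does selective circuit end distort the paired difference?** Simulation of 200,000 patients with assumed inputs: pilot means; patient SD 0.12, session SD 0.12, reading SD 0.08; session levels floored at 0.1 mmol/L, which makes the true difference 0.127 rather than 0.135; circuit-end hazard 0.06 per interval at iCa 0.35; no replacement circuits. Log hazard rises by 0, 0.2 or 0.4 per 0.1 mmol/L. In the titrated case, whenever a reading exceeds 0.40, 30% of its excess over 0.35 is removed before the next reading. The column for all circuits is the difference had every circuit run on.

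| Scenario at 48 h | All circuits | Complete pairs | Pairs left |
|---|---|---|---|
| End unrelated to iCa, no titration | 0.127 | 0.127 | 38% |
| Log hazard +0.2, no titration | 0.128 | 0.119 | 35% |
| Log hazard +0.4, no titration | 0.127 | 0.107 | 31% |
| Log hazard +0.4, titration | 0.054 | 0.061 | 39% |

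Without titration the difference is understated. With titration it is overstated, by 0.061 - 0.054 = 0.007.

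**4. Titration closer to Table 1.** A second simulation used SD 0.2 per mode, correlation 0.5, a 5% chance of circuit end per 6 h at iCa 0.305 with odds multiplied by 1.5 to 2 per 0.1 mmol/L, and the Table 1 steps. It assumed that iCa falls by 0.0005 to 0.002 mmol/L per ml/h of citrate. The bias at 24 h ran from about -0.015 to +0.002 mmol/L. For scale, the standard error with 26 pairs is 0.2 / √26 = 0.039.

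**5. Which readings are affected.** Data collection and follow-up fixes the all-site measurement at 2 h after the start of each new circuit, when nearly all circuits should still be running. Post-filter and systemic iCa are then monitored every 2 h, or every 4 to 6 h once on target. No later pre-filter or effluent calcium reading is specified. The problem therefore concerns post-filter and systemic iCa after 2 h.

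**The case against.** **The method is assembled from two sections.** Statistical analysis does not say that the paired tests are repeated at each time point; that phrase comes from a limitations sentence about combined modes. The Discussion also promises blood pH, acid-base status and phosphate as covariates, which a paired t-test cannot take, so some model is foreseen and its detail may sit in an unseen analysis plan. This stands in part. But the article does name tests for its longitudinal outcome, and those covariates do not deal with a session that has ended. Clotting and filter lifetime are recorded, yet no stated analysis links them to iCa.

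**Replacement circuits.** A clotted circuit may be followed at once by a new one, with its own 2 h measurement, so clotting need not remove later data in that mode. This stands, and it makes the pair counts above pessimistic. The text does not say whether the new circuit continues the old time axis or starts another.

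**Direction.** A reader might infer that high-iCa CVVHD circuits leave first, giving a false downward trend and late differences pulled towards zero. That follows only if iCa is left untitrated. Table 1 adjusts citrate whenever post-filter iCa is off target; under a normal distribution with mean 0.44 and SD 0.2, 48% of CVVHD circuits would start above 0.45. With titration the bias takes either sign.

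**Power.** A reader might also infer power of about 42% to 61% at 24 h, from 11 to 14 remaining pairs. That rests on an assumed circuit-end rate, with no titration and no replacement. The documents support neither those figures nor a claim that the sample size is wrong.

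**Conclusion.** The concern holds for the later time points and the trend. Paired tests hour by hour suit this outcome poorly: they discard readings from any patient with one ended session, and they compare a subset that shrinks over time and may be selected by mode and outcome under the protocol's own hypothesis.

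Its size cannot be derived from the documents, which give no circuit survival and no dose-response of iCa to citrate. Under the assumptions shown, the bias with titration is small beside a standard error of 0.039 and its sign is not fixed. The loss of pairs could matter more, with power from 92% down to 33% over the assumed survival range. The calculation of 26 is correct where about 26 complete pairs remain, and the 2 h comparison is nearly unaffected. This is an improvement worth making before the data are analysed; it does not invalidate the study.

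**What to change.** In Statistical analysis:

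- Base the confirmatory comparison on the 2 h post-filter iCa reading, to which the 26 pairs can reasonably apply.
- Analyse the trend with one linear mixed model on all available post-filter and systemic iCa readings, fitted separately for each: mode, period, time and mode-by-time as fixed effects; patient and session within patient as random effects. SPSS 23 offers this as MIXED. It keeps the readings taken before a session ended.
- State whether a replacement circuit restarts the time axis or continues it.
- Report, for each time point, the number of complete pairs and the reasons circuits ended, by mode.
- Add one sensitivity analysis for circuit end, because the model assumes that ending depends on recorded readings.

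The cost is analysis wording and one extra analysis. No new patients or measurements are needed; clotting events and filter lifetime are already collected.

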## Ethics and dissemination

### Ethical approval and informed consent

The study protocol and consent forms were approved on 7 July 2023 by the Ethics Committee of Fujian Provincial Hospital (Approval #K2023-07-007). Protocol amendments (if any) will be approved by the Ethics Committee.

Following the screening process, a designated study coordinator will be introduced to the family by the ICU physician. The study coordinator’s credentials will be clearly communicated to the family to establish trust and credibility. The study coordinator will provide a comprehensive explanation of all relevant aspects of the project, pausing frequently to address any questions or concerns the family may have. In addition, the coordinator will ask the family to summarize the information discussed in their own words to ensure understanding.

During the discussion, it will be emphasized that participation in the study is completely voluntary and that the family has the right to refuse consent without any consequences. The coordinator will also emphasize that the family can withdraw their consent at any time during the study. To ensure proper documentation, written consent will be obtained in the presence of a witness.

### Dissemination of results

No interim analysis is planned for this study. The results will be submitted to an international peer-reviewed journal for publication. Additionally, the findings will be shared through national and international scientific conferences to disseminate the research to a wider audience. The corresponding authors will make the data sets from this study available to interested parties upon a reasonable request.

## Data Availability

No data were generated in this work as this is a study protocol.
